### Screening

Questions about a child’s age, individualized education plan (IEP), medical history, safety to complete exercise (PAR-Q), and ADHD status are asked in an initial phone screen. Only children who meet these criteria remain eligible and are scheduled for the first day of testing. On the first day of testing, children are screened for IQ scores and Tanner status.

### Day 1 procedure

At the first visit, participants and their legal guardians complete a detailed health and demographic questionnaire, pre-participation health screening questionnaire, the ADHD Rating Scale IV, the Pittsburg Sleep Quality Index questionnaire, and the modified Tanner pubertal self-assessment questionnaire [23]. Parents/guardians are given the option of taking home the pubertal self-assessment questionnaire in case they prefer that their spouse complete the form or if they would rather respond to it at home. A trained experimenter administers the Edinburgh Handedness Inventory to the child. The child is then administered the KBIT-2 [24] to measure their intelligence quotient (IQ). All tests are entered into a database by staff, from which standardized scores and percentiles are created. Participants who meet all inclusion criteria are invited to participate in three additional days of testing. The first session lasts approximately 2.5 h.

#### Intelligence assessment

Children complete the Kaufman Brief Intelligence Test-2 (KBIT-2) [24] to assess intelligence. The KBIT-2 is a commercially available paper and pencil-based assessment of cognitive abilities that has been age normed.

#### Cardiorespiratory fitness (CRF) measurement

Children complete a VO_2_max test on a motorized treadmill (Treadmill: Trackmaster TMX428; Metabolic cart: COSMED Quark CPET OMNIA, Concord, CA) using a modified Balke protocol at the end of their first session. This test is conducted based on recommendations from the American College of Sports Medicine. Three trained, first-aid and CPR-certified, experimenters will conduct the exercise test. Participants complete a brief warmup and then run at a constant speed with incremental intensity increases through grade inclines of 2.5% every 2 min until volitional fatigue. The speed is determined based on the child’s height, running stride, and overall ability of the child. Participants wear a heart rate (HR) monitor during the test to determine maximal heart rate. Ratings of perceived exertion (RPE) are assessed every 2 min using the children’s OMNI scale [25]. Relative peak oxygen consumption is expressed in ml/kg/min and based upon maximal effort as evidenced by (1) a plateau in oxygen uptake corresponding to an increase of less than 2 ml/kg/min despite an increase in exercise workload, (2) a peak HR ≥ 185 bpm [26, 27] and a HR plateau [26], (3) RER ≥ 1. 0 [28], and (4) ratings on the children’s OMNI scale of perceived exertion ≥8 [25]. Age- and gender-matched percentile values will be derived by using normative values [29]. In order to reduce collinearity between whole body adiposity and aerobic fitness, fat-free VO_2_max (ml/kg lean/min) will be calculated using an individual’s absolute VO_2_max and lean mass. This measure has greater validity than when comparing aerobic fitness in children of different body sizes [30].

#### Dual-energy X-ray absorptiometry

Previous research suggests that body composition can influence cognition and brain function and may influence the mechanisms by which cognitive changes occur following acute exercise. Thus, we collect body composition measures to determine if they serve as mediator variables. Height and weight are measured and body mass index (BMI) is calculated by dividing body mass (kg) by height (m) squared. Dual-energy X-ray absorptiometry (DXA) (GE Lunar iDXA, Madison, Wisconsin) measures bone mineral content, density, and whole-body and regional soft tissue composition. Participants are instructed to wear or change into shorts and a T-shirt containing no metal. Participants lie on their back on the DXA table for about 10 min, remaining motionless with their eyes closed. The DXA can separate body mass into fat and lean measures, allowing for the evaluation of fat mass without the confounding influence of other tissues.

#### Psychosocial assessments

##### ChEAT

The ChEAT-26 is a 26-item, self-report questionnaire that measures the level of atypical and disordered eating attitudes and behaviors. Respondents answer each of the EAT items using a 6-point Likert-type scale and indicate how frequently (1 = never; 6 = always) they experience various thoughts, feelings, or behaviors in relation to eating.

##### Children’s Depression Inventory 2 (CDI 2)-Short Version

The CDI is used to screen for depressive symptoms. The CDI is widely used to assess depressive symptomatology in children and adolescents aged 8–17 years. The scale is composed of 12 Likert-type items scored from 0 to 2, with higher scores reflecting more important depressive symptomatology.

##### State and Trait Anxiety Inventory for Children (STAIC)

The STAIC is made up of 2 scales of 20 items each, describing psychological manifestations of anxiety; the State scale describes the current state of anxiety, and the Trait scale describes a general propensity to react with anxiety to stressful events. Each item is scored from 1 to 3, the total score for each scale thus ranging from 20 to 60.

#### Days 2–4 procedure

At intervention visits (days 2, 3, and 4), the participant engages in the same protocol each day, with the sole exception of a different intervention each day. At the start of each visit, children are outfitted with a heart rate monitor to measure the intensity of the intervention. Upon entering the laboratory, children are asked to sit quietly for 10 min to allow their heart rate to return to baseline levels, after which they provide the first saliva sample by drooling into a tube. Participants are then fitted with an EEG cap. Next, they complete cognitive tasks on a computer while EEG data is simultaneously collected. Then, the child completes one intervention at each visit: (1) aerobic exercise, (2) quiet resting, or (3) the TSST. Upon completion of the intervention, participants provide another saliva sample. Participants then complete the same cognitive tasks again while EEG data is simultaneously collected. Participants will provide another saliva sample, and then they will complete an academic achievement test. At the end of the visit, the final saliva sample is collected. Visits 2–4 last approximately 2.5 h each. At the conclusion of study participation, no further ancillary or post-trial care was offered.

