	**Days 2–4 protocol**
0–10 min	10-min rest/baseline
10–25 min	EEG cap preparation
25–30 min	Baseline saliva sample
30–45 min	Pre-intervention cognitive tasks
	Interventions
45–60 min	*Trier*
45–70 min	*Aerobic and rest*
70–75 min	Post-intervention saliva sample
75–90 min	Post-intervention cognitive tasks
90–95 min	Post-cognitive task saliva sample
95–115 min	Academic achievement testing
115–120 min	Intervention completion saliva sample

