#### Academic achievement testing

##### Wide Range Achievement Test 4 (WRAT4)

Participants complete the WRAT-4 assessment tests for reading (the number of words pronounced correctly) and mathematics (the number of mathematical computations completed correctly). The WRAT-4 is a commercially available paper and pencil based academic achievement assessment that has been age normed. The WRAT allows for repeated administration through the use of two equivalent forms. Administration of the WRAT-4 is conducted by trained experimenters with the duration of the assessment lasting ~ 30 min. Each child completes one version of the WRAT-4 following their rest session, and one version of the WRAT-4 following either their aerobic or TSST session, since only two versions of the task exist.

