Children are asked not to eat a major meal; consume food high in caffeine, sugar, or acidity; or brush their teeth for at least an hour before the session. In order to control for diurnal variation, each child’s sessions are scheduled at the same time of day. They are also asked to report the presence of any oral disease or injury, and whether or not they consumed any medications within the 12 h prior to the sessions. Adherence to these protocols is confirmed before beginning any sessions. If children have not followed the pre-testing protocols, enough time is passed to allow the protocol to be followed, or the child is rescheduled. Before the first collection of each visit, participants are instructed to swallow and rinse with water to clear the mouth of all saliva. Children are then not allowed to have anything to eat or drink throughout the rest of the session. Salivary samples for evaluation of sAA and CORT are collected throughout the intervention sessions. Specifically, samples are collected at baseline (after 10 min of baseline sitting), prior to (PRE), and immediately following experimental manipulation (i.e., exercise, TSST-C, rest), ERP/cognitive testing, and academic achievement testing (see Experimental Timeline).

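### The three intervention visits are called identical apart from the intervention, but the WRAT-4 always follows rest and is left out of one exercise or TSST visit per child, so what precedes the final saliva sample depends on condition

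*Protocol article*

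**What the plan says.** Under Days 2–4 procedure, the protocol article says that at the intervention visits "the participant engages in the same protocol each day, with the sole exception of a different intervention each day". The sequence that follows makes no exception by condition. After the post-intervention cognitive tasks, "Participants will provide another saliva sample, and then they will complete an academic achievement test", and then "At the end of the visit, the final saliva sample is collected". The participant timeline (Table 2) gives a single Days 2–4 schedule. It lists "Academic achievement testing" at 95–115 min and "Intervention completion saliva sample" at 115–120 min.

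The WRAT-4 section describes something else. Every child takes the test after rest, but for the other two conditions the section provides only for "one version of the WRAT-4 following either their aerobic or TSST session, since only two versions of the task exist".

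The saliva section gives four timepoints, the last at the end of the visit. It also lists sampling "immediately following experimental manipulation (i.e., exercise, TSST-C, rest), ERP/cognitive testing, and academic achievement testing".

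The analytic strategy uses baseline sAA and cortisol levels (i) and sAA change (s) as mediators, puts cortisol change into the same model, and compares sAA between conditions. It does not say which samples define the change.

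**The concern.** Two forms of the WRAT-4 cannot cover three sessions, so every child has one session without it, and by rule that session is never rest. The visits therefore differ in a second respect besides the intervention, and that difference is associated with condition by design.

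It matters for the fourth saliva sample. The article gives reason to think an academic test could move sAA: the Background says sAA responds to psychosocial stress, and the TSST itself includes mental arithmetic in front of observers. The WRAT-4 is a reading and mathematics test administered by an experimenter. If it shifts sAA or cortisol, a comparison of final samples between exercise and rest mixes the effect of the intervention with the presence of the test. The Summary of aims claims that changes under exercise can be attributed to exercise rather than to other factors. For the final sample, that claim depends on the sameness statement being true.

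**Working it through.** There is no stated figure to reproduce. The check tabulates test exposure before the final sample and works out what follows.

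**Inputs.** 103 children (Summary of aims). WRAT-4 after every rest session and after one of the two other sessions (WRAT-4 section). Saliva slots at 25–30, 70–75, 90–95 and 115–120 min (Table 2). Assumed, because not given: p, the share of children whose second WRAT-4 follows exercise (0.5, range 0.4 to 0.6), and delta, the shift the test causes in the final sample.

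**Exposure.**

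| Session | Final samples preceded by the WRAT-4 |
|---|---|
| Rest | 103 of 103 |
| Exercise | 103p: 51.5 at p = 0.5 (41.2 to 61.8) |
| TSST | 103(1 − p): 51.5 at p = 0.5 (61.8 to 41.2) |
| Exercise and TSST together | 103 of 206, whatever p is |

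**Bias in contrasts on the final sample.**

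| Contrast | Formula | p = 0.4 | p = 0.5 | p = 0.6 |
|---|---|---|---|---|
| Exercise − rest | (p − 1) delta | −0.6 delta | −0.5 delta | −0.4 delta |
| TSST − rest | (1 − p − 1) delta = −p delta | −0.4 delta | −0.5 delta | −0.6 delta |
| Exercise − TSST | (2p − 1) delta | −0.2 delta | 0 | +0.2 delta |

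**If change were a straight-line slope through all four samples** (an illustration; the article does not say this). The slot mid-times are 27.5, 72.5, 92.5 and 117.5 min, with mean 77.5. The deviations are −50, −5, 15 and 40, and their squares sum to 2500 + 25 + 225 + 1600 = 4350. The last sample has weight 40/4350 = 0.0092 per min, or 0.83 over the 90-min span. The exercise–rest bias in change over that span is 0.83 × (−0.5) = −0.41 delta (−0.50 to −0.33 delta for p = 0.4 to 0.6).

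**Can the two effects be separated?** Take a model with child, condition and a WRAT-given indicator, 102 children, an even split and residual variance σ².
- The indicator is estimated by comparing the exercise − TSST difference between children tested after exercise and children tested after TSST. The two group means differ by 2 delta, with variance 2σ²(1/51 + 1/51) = 4σ²/51, so the estimate of delta has variance σ²/51 = 0.0196σ².
- The unadjusted exercise − rest contrast has variance 2σ²/102 = 0.0196σ². Adjustment adds 0.25 × 0.0196σ² = 0.0049σ².
- The variance ratio is 0.0245/0.0196 = 1.25.

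The design matrix has full rank (105 of 105), so the effects are separable, at the price of a quarter more variance for that contrast. Because rest never occurs without the test, this relies on the test effect being the same after rest as after the other two conditions.

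**The case against.** The strongest reply is that only the wording is shown to be wrong. The analytic strategy does not say that sAA change uses the fourth sample, and the choice of samples for a derived variable is commonly left to an analysis plan. The article's own reasoning points away from that sample: it describes phasic activation as brief and rapid, and the fourth sample comes after every cognitive, EEG and academic outcome has been collected. The other three precede the academic test and are untouched. Sessions without the WRAT-4 also yield no WRAT-4 score, so any analysis restricted to sessions with a score has the test throughout. Most of this stands. It makes the consequence for mediation conditional, but does not remove it, because nothing excludes the fourth sample and the Discussion speaks of sAA and cortisol trajectories.

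Two inferences a reader might draw are not supported. One is that in the untested session the final sample is taken earlier: Table 2 gives it a fixed slot, and the article does not say what fills the preceding time. The other is that the stress of a timed test is at issue: the WRAT-4 section gives scores as numbers correct and an approximate duration, and does not call the test timed.

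It is also fair to say that delta has no value in the document and could be negligible.

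**Conclusion.** The contradiction is definite: the sameness statement and the single timeline cannot both stand with the WRAT-4 section. It also follows that exposure to the academic test before the final saliva sample depends on condition, 100% after rest against 50% over exercise and TSST combined. Randomising the order of interventions does not balance this.

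The resulting bias on the fourth sample is about −0.5 delta for each contrast with rest at an even split. It is zero for exercise against TSST only if the split is exactly even. This rests on an unstated split and an unknown delta; the slope figure of −0.41 delta further assumes a linear change through four samples.

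A reader might conclude that the mediator, and so the effect of exercise on sAA, is confounded outright. The document does not support that. The association is partial, affects one sample of four, can be separated under an additive model, and reaches the mediation analysis only if the change measure includes that sample. The point is worth acting on because the protection is cheap and the sameness claim underpins the article's attribution of effects to exercise.

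**What to change.** 1. Reconcile Days 2–4 procedure, Table 2, the WRAT-4 section and the saliva section, so that all say which sessions include the WRAT-4, how the tested session is chosen between exercise and TSST, and what precedes the final sample when there is no test.
2. Define sAA and cortisol change, for the mediation models and the condition contrasts, from the baseline, post-intervention and post-cognitive-task samples. All three precede the academic test in every session. This also keeps the mediator ahead of the academic outcome in time.
3. Use the fourth sample only in a secondary model with a session-level indicator for WRAT-4 given or not. The adjustment is clean only if the tested active session is chosen at random; state whether it was.

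The change is to wording and analysis definitions, with no new visits or procedures. The cost is one fewer sample in the main change measure and, in the secondary model, a variance ratio of about 1.25 for exercise against rest at an even split. Adding a filler activity to remaining untested sessions is not needed: it would be a procedural change requiring ethics approval, and could make the fourth sample differ between earlier and later children.

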#### Interventions

Children are asked not to exercise or participate in structured physical activity prior to attending any of their sessions, and this is verified via self-report before each intervention session. Maximal heart rate (HRMax) is determined from the maximal exercise test completed on day 1 and is used to determine relative exercise intensity for days 2, 3, or 4. The interventions will be completed in a randomized crossover design, such that participants will act as their own controls, through initial randomization to condition assignment and condition counterbalancing across participants. With 3 interventions, there are a total of 6 different interventions (for example, aerobic-TSST-rest, aerobic-rest-TSST, TSST-rest-aerobic, TSST-aerobic-rest, rest-aerobic-TSST, rest-TSST-aerobic). A random number generator will be used to determine which intervention order a participant receives. See Table 2 for participant timeline.

**Table 2 Tab2:** Participant timeline

Time schedule	Activity
6–30 months	Participants Enrolled
Approximately 1 week prior to intervention 1	Day 1
	**Days 2–4 protocol**
0–10 min	10-min rest/baseline
10–25 min	EEG cap preparation
25–30 min	Baseline saliva sample
30–45 min	Pre-intervention cognitive tasks
	Interventions
45–60 min	*Trier*
45–70 min	*Aerobic and rest*
70–75 min	Post-intervention saliva sample
75–90 min	Post-intervention cognitive tasks
90–95 min	Post-cognitive task saliva sample
95–115 min	Academic achievement testing
115–120 min	Intervention completion saliva sample

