##### Aerobic

To assess the effect of a single bout of aerobic exercise on executive control, we use an exercise stimulus based on the American College of Sports Medicine guidelines for improving aerobic capacity, which consists of 21 min of exercise on a treadmill at 70–75% of the individual’s maximum heart rate. Participants engage in a 1-min warmup and a 1-min cooldown, with the majority of time (i.e., 19 min) spent exercising at 70–75% of HRmax. Participants’ exercise on a motor-driven treadmill at a constant speed during the 19-min period. Based on fitness level and participant ability, they may walk or run. Once the desired speed is set, the incline is adjusted to reach the desired intensity.

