##### Trier Social Stress Test for children (active control)

Children participate in a modified laboratory stress protocol based on the TSST for children [31]. The TSST for children consists of a speech task in which children talk about themselves and complete a mental arithmetic task in front of a camera (which does not record the session, but is there simply to induce stress) and three neutral observers. Specifically, participants are asked to imagine that they are in a new class with 20 other students, and that their teacher has asked them to stand in front of the class and introduce themselves. Children are instructed to speak for 6 min about themselves, their personality, and why they believe that they would be liked by their classmates. In addition, they are asked to discuss at least one good and one bad aspect of themselves. The mental arithmetic task entails asking children to serially subtract the number 5 from a larger number as quickly as possible for 4 min. The TSST for children lasts approximately 14 min. Although the TSST for children is shorter in duration than the exercise task, prior research has shown that it successfully elevates sAA and CORT levels [32].

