##### Rest (passive control)

Participants sit in a comfortable chair, placed in the same room as the motor-driven treadmill, for 20 min. Children are asked to sit quietly or read a book of their choosing (excluding schoolwork). They are instructed to minimize conversation.

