#### Saliva collection (sAA and cortisol)

Salivary samples for evaluation of sAA and cortisol are collected throughout the experimental manipulation at 4 timepoints. These collection timepoints include: before cognitive testing begins/baseline, following the intervention, following post-intervention cognitive tasks, and at the completion of the visit. At each collection time, participants are seated comfortably, leaning forward with arms crossed in front of them. Unstimulated salivary samples (at least 2 mL) are collected by the passive drool technique over a 2-min period. Samples are collected into pre-weighed saliva collection tubes and immediately placed on ice. After weighing collection tubes for quantitation of saliva volume and determination of flow rate ([post-collection tube weight − pre-collection tube weight]/2 min), samples are aliquoted and frozen at − 80 °C until analysis. sAA and cortisol are packaged, shipped on dry ice, and analyzed at the University of Ottawa. sAA and cortisol are measured using commercially available kits (α-amylase Saliva Enzymatic Assay and Cortisol Saliva ELISA, IBL International, Hamburg, Germany) according to manufacturer’s instructions. Briefly, on the day of analysis, saliva samples are thawed, centrifuged at 1500×*g* for 15 min at room temperature to remove cellular contaminants and debris. For sAA, samples are diluted 1:301 in diluted sample buffer, and read in a microplate reader (POLARstar Omega, BMG Labtech, Guelph, Canada) at 22 °C at a wavelength of 405 nm at 3 and 8 min after incubation at room temperature. For CORT, samples are incubated with enzyme conjugate solution at room temperature for 2 h, washed, incubated with enzyme substrate solution at room temperature for 30 min. After the addition of the “Stop Solution” to end the enzyme/substrate reaction, samples are read in a microplate reader (POLARstar Omega, BMG Labtech, Guelph, Canada) at 450 nm within 15 min. All samples are analyzed at least in duplicate.

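### Table 2 sets one clock time for post-intervention saliva and cognitive tasks although the TSST ends earlier, which conflicts with the text and, if followed, ties a longer delay to the TSST.

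*Protocol article*

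**What the plan says.** The Days 2–4 part of Table 2 is a running clock from arrival. The intervention starts at 45 min in every condition. The Trier slot closes at 60 min; aerobic and rest share a slot that closes at 70 min. The rows after that are common to all conditions: "Post-intervention saliva sample" at 70–75 min and "Post-intervention cognitive tasks" at 75–90 min. No row covers 60–70 min on a TSST day.

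The text ties the sample to the intervention itself. The Days 2–4 procedure states: "Upon completion of the intervention, participants provide another saliva sample". The saliva section says that samples are taken "immediately following experimental manipulation" and lists exercise, TSST-C and rest as the manipulations meant.

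The durations in the text are:
- TSST: "The TSST for children lasts approximately 14 min".
- Aerobic: the condition is described as one "which consists of 21 min of exercise on a treadmill at 70–75% of the individual’s maximum heart rate".
- Rest: the child sits in a chair "placed in the same room as the motor-driven treadmill, for 20 min".

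The TSST section acknowledges that the stressor is shorter than the exercise. It answers only that the TSST still raises sAA and cortisol, and says nothing about a wait before sampling.

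The baseline sample is also placed in two ways. The Days 2–4 procedure puts it before the EEG cap is fitted. Table 2 puts cap preparation at 10–25 min and baseline saliva at 25–30 min, after the cap.

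**The concern.** The Summary of aims describes the mediator as phasic sympathetic activation, that is, short-lived and fast. The Power and analytic strategy section plans to ask whether sAA is larger after exercise than after the TSST or rest, and to compare outcomes regressed on sAA at the same time. The TSST is the active control, meant to separate exercise from stress and raised heart rate.

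If the TSST sample is taken later after the end of its intervention than the exercise sample, a fast-fading marker has had more time to fall. Two equal responses could then look like a larger response to exercise. The same holds for the cognitive tasks if arousal fades before they start. The delay belongs to the condition, so neither the randomised order nor the within-child comparison removes it.

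**Working it through.** **Inputs.** From Table 2: intervention start 45 min; Trier slot end 60; aerobic and rest slot end 70; saliva row starts 70; task row starts 75. From the intervention sections: TSST about 14 min, aerobic 21 min, rest 20 min.

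**Formula.** Delay = start of the post-intervention row − end of the intervention. It is computed once with the slot ends and once with the text durations (end = 45 + duration), without mixing the two sources.

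| Condition | Slots: to saliva | Slots: to tasks | Text: to saliva | Text: to tasks |
|---|---|---|---|---|
| TSST | 70 − 60 = 10 | 75 − 60 = 15 | 70 − 59 = 11 | 75 − 59 = 16 |
| Aerobic | 70 − 70 = 0 | 75 − 70 = 5 | 70 − 66 = 4 | 75 − 66 = 9 |
| Rest | 70 − 70 = 0 | 75 − 70 = 5 | 70 − 65 = 5 | 75 − 65 = 10 |

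**Excess delay for the TSST.** On the slots it is 10 − 0 = 10 min against both other conditions. On the text durations it is 11 − 4 = 7 min against aerobic and 11 − 5 = 6 min against rest. The same differences apply to the tasks (15 − 5 = 10; 16 − 9 = 7; 16 − 10 = 6). Aerobic against rest differs by 0 min (slots) or 1 min (text).

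**What that could mean for sAA (illustration only).** The document gives no rate of return to baseline. Assume that the rise above baseline decays exponentially with half-life h, so that the fraction left after an extra delay d is 0.5^(d/h):

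| Assumed h (min) | d = 6 | d = 7 | d = 10 |
|---|---|---|---|
| 5 | 44% | 38% | 25% |
| 10 | 66% | 62% | 50% |
| 20 | 81% | 78% | 71% |
| 30 | 87% | 85% | 79% |

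These percentages apply to the rise, not to the sAA level. The ratio of levels between conditions would be closer to 1.

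**Can a covariate repair it?** On the slots, the delay to saliva is 10 min on every TSST visit and 0 on every other visit. It is then exactly 10 × the TSST indicator, and a model cannot separate the two. Small departures from the clock would make them nearly, rather than exactly, collinear.

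**The case against.** The strongest reply is that Table 2 is a simplified clock. Two alternative interventions overlap in it, and the later rows naturally follow the longer one. Two places in the text tie the sample to the end of the intervention, one of them naming the TSST, so staff may simply move the TSST-day rows forward. Other slots also look nominal: the achievement test is described as taking about 30 min but has a 20-min slot. This stands as a limit. A reader might infer that children do wait 10 min and that the exercise–TSST contrast is already biased. The document does not show that; it shows two incompatible instructions, one of which would produce the bias. Nor does it say that the table is simplified.

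A reader might also infer that the cognitive tasks contradict the word immediately. They do not: that wording concerns saliva only, and for the tasks the issue is unequal delay. Nor can a definite fold-difference in sAA be claimed, because it would rest on an assumed half-life.

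There is also a case for the table as written. It equalises time from intervention onset to sample and from pre-test to post-test, which could matter for cortisol and for test spacing. The document does not give this as its reason, but the trade-off is real.

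Finally, the saliva section says that samples "are collected throughout the experimental manipulation at 4 timepoints" and then gives a list that can be read as five, and the task and visit lengths fit the clock loosely. These are side issues, common to all conditions, and cannot create an exercise–TSST difference.

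**Conclusion.** The contradiction between Table 2 and the two text sections holds and needs no assumption. The confounding is conditional: it arises if the table's clock is what is followed. In that case TSST saliva and tasks come 10 min (slots) or 6–7 min (text durations) later after the end of the intervention than in the other conditions, and the planned exercise–TSST contrasts in sAA and cognition carry that delay. The direction for sAA, towards a larger apparent exercise response, assumes a marker that is falling by then; the amount cannot be fixed from the document. Exercise versus rest is essentially untouched. The point is worth correcting because data collection was ongoing at publication and the remedy is cheap.

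**What to change.** - Reconcile Table 2 with the Days 2–4 procedure and the saliva section. Set the post-intervention saliva sample and the start of the cognitive tasks at the same number of minutes after the end of the intervention in all three conditions.
- Give the TSST day its own rows. Keeping the table's slot lengths, saliva would fall at 60–65 min and the tasks at 65–80 min, and the excess delay on the slots would be 0.
- State whether the baseline sample comes before or after the EEG cap, and use that one sample at every visit as the reference for sAA change.
- Use actual collection times, not the nominal clock, in the sAA trajectory model.
- For visits already run on the table's clock, report the unequal delay as a limitation of the TSST contrasts. A lag covariate is nearly collinear with condition and should not be presented as a repair.

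**Cost.** Table and procedure wording, plus a recorded time for each sample. The downside is that other intervals become unequal. On the slots, onset to saliva would be 60 − 45 = 15 min on TSST days against 70 − 45 = 25 min otherwise. The end of the pre-test to the start of the post-test would be 65 − 45 = 20 min against 75 − 45 = 30 min. The protocol should state that this trade-off is accepted.
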